### Sampling

To calculate the sample size needed for this cross-sectional study, the data from a previous study (which estimated the prevalence of harmful alcohol consumption among women in Juiz de Fora as approximately 9.1 %) will be considered [48]. In addition, this study considered a maximum measurement error of 3 %, 95 % confidence intervals, a finite population correction based on the number of women residing in the randomly selected neighborhoods (consistent with the 2000 IBGE census), an effect of the sampling design equal to 2, and a 25 % refusal to participate rate. Thus, the initial sample size was estimated as 824 respondents (412 in each neighborhood).

To calculate the clinical trial sample size, the following considerations will be made: (i) a significance level of 5 %; (ii) a statistical power of 80 % (to compare proportions of the two independent groups); (iii) a non-interview rate of 15 % due to refusal to participate or failure to locate the informant; (iv) the effect of the BI after 3 months (i.e., an expected reduction of at least 20 % in the number of women with harmful alcohol consumption; and (v) an effect of the sampling design equal to 2. Thus, the calculated sample size for each group (i.e., the treated group [TG] and control group [CG]) will be 73 women.

To make the second study possible, considering the prevalence of women with risky alcohol consumption in the two neighborhoods surveyed around the estimated above (ie, 9.1 %), there will be necessary an increase in the sample size for Study 1, which now has approximately 1600, with 800 in each of the neighborhoods.

To recruit the women who belong to the target population, a two-stage cluster sampling method will be adopted. The streets belonging to each neighborhood will be considered as primary sampling units (PSUs), and households will be considered as secondary sampling units (SSUs). To select PSUs, a simple random sampling method without replacement will be adopted, whereas the SSUs will be selected using systematic sampling. In each selected household, the field researchers will invites all women who met the inclusion criteria to participate in the study.

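### The enlarged Study 1 size of about 1600 carries no refusal allowance: it supplies 2 × 73 trial women only if all 1600 are interviewed, and about 109–116 if 1600 counts women approached

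*Protocol article*

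**What the plan says.** All the relevant text is in the Sampling section of the protocol article.

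- **First survey size.** The inputs are a prevalence of 9.1 %, "a maximum measurement error of 3 %, 95 % confidence intervals", a finite population correction, a design effect of 2 and "a 25 % refusal to participate rate". From these, "the initial sample size was estimated as 824 respondents (412 in each neighborhood").
- **Trial size.** The inputs are 5 % significance, 80 % power, 15 % non-interview, a reduction of at least 20 % in women with harmful consumption, and a design effect of 2. The result for each group "will be 73 women", so 146 in total.
- **Enlarged survey size.** The reason given is the trial's need, "considering the prevalence of women with risky alcohol consumption in the two neighborhoods surveyed around the estimated above (ie, 9.1" %). The result is "an increase in the sample size for Study 1, which now has approximately 1600", split as 800 per neighbourhood.

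The last step cites prevalence only. It mentions no refusal rate and does not say whether 1600 counts women approached or women interviewed. Under Study 2, women scoring 8 or more on the AUDIT in the survey are the only source of trial participants.

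**The concern.** The survey was roughly doubled for one purpose, to find enough women for the trial. The number chosen for that purpose appears to have lost the refusal allowance that its predecessor carried. An AUDIT score exists only for women who complete the interview, so prevalence has to be applied to interviews and not to women sampled.

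If 1600 is the number to be drawn and approached, the trial would be about 20–25 % smaller than planned before any loss to follow-up. If it is the number to be interviewed, the field sample has to be about a quarter to a third larger than the only figure given. The two readings imply different numbers of streets and households to select, so the point needs settling before sampling.

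**Working it through.** **Inputs, all from Sampling:** prevalence 0.091; margin 0.03 at 95 % confidence; survey design effect 2; survey refusal 25 %; trial 73 per group; trial non-interview 15 %; trial design effect 2; enlarged survey about 1600.

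**1. Reproduce the 1600.**

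- 2 × 73 = 146 women needed.
- 146 / 0.091 = 1604, and in reverse 1600 × 0.091 = 145.6.

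The stated figure is reproduced exactly with prevalence alone, so there is no room in it for refusal.

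**2. Check that the 824 includes refusal.** The text lists refusal among its inputs, and the arithmetic agrees if the 3-point margin is taken to apply to both neighbourhoods combined (an assumption):

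- 1.96² × 0.091 × 0.909 / 0.03² = 353
- × 2 (design effect) = 706

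A finite population correction can only lower 706, so 824 cannot be reached without the refusal inflation. With it, the figure before the correction is 706 / 0.75 = 942, or 706 × 1.25 = 883. A correction that brings either down to 824 is possible. The population count is not given, so this cannot be checked further.

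**3. Put 1600 on the same scale as the 824.** The article does not say whether refusal was handled by dividing by 0.75 or multiplying by 1.25, so both are shown.

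| Convention | Interviews from 1600 | Women with AUDIT ≥ 8 | Per group | Approaches needed for 146 |
|---|---|---|---|---|
| Divide by 0.75 | 1600 × 0.75 = 1200 | 1200 × 0.091 = 109 | 55 | 1604 / 0.75 = 2,139 |
| Multiply by 1.25 | 1600 / 1.25 = 1280 | 1280 × 0.091 = 116 | 58 | 1604 × 1.25 = 2,005 |

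Milder refusal also misses the target: at 10 %, 15 % and 20 % refusal, 1600 approaches yield 131, 124 and 116 women.

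**4. Does another allowance absorb the loss?** The 15 % non-interview rate is already an input to the 73, so using it again for survey refusal would count it twice. The article gives no rule for replacing refusers or for continuing until 146 women are found.

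**5. Illustrative power.** No control-group rate is stated. Assuming 100 % against 80 % at three months, with a two-sided 5 % test, comes close to reproducing 73:

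- (1.96 + 0.84)² × (0 + 0.16) / 0.20² = 31.4
- 31.4 × 2 × 1.15 = 72.2, rounded up to 73 (dividing by 0.85 instead gives 73.9)

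The effective number per group is then n × 0.85 / 2. The lower power figure uses the pooled variance under the null, the higher one the unpooled variance:

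- At 73: effective 31.0, power 76–80 %.
- At 54.6 (the 55 above): effective 23.2, power 63–67 %.

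**The case against.** The strongest reply is that 1600 means completed interviews. The 824 are called respondents, the abstract gives 1600 as the size of the household sample, and the near-exact match of 1600 × 0.091 with 146 is what one would see if prevalence had been applied to women who answered. On that reading the trial gets its 146, and the number to approach is fieldwork detail that a condensed article might leave out.

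This reading is possible and cannot be excluded. It therefore rules out an inference that a reader might draw, that the survey cannot be expected to supply the trial. The documents show an undefined unit and a shortfall under one reading of it, not a proven shortfall. The reply does not clear the section, however. The same sentence that calls the 824 respondents lists a refusal rate among the inputs, and that rate serves only to turn interviews into women to approach. The 1600 is then presented as an increase on that number. If the unit changed between the two paragraphs, the article does not say so.

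Two other tempting inferences also fail:

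- **Power.** A reader might take 63–67 % as the power on the plan's own assumptions. The 100 % against 80 % is a back-calculation. A control rate of exactly 100 % has no variance, and a normal approximation at an effective 23 per group is rough.
- **Prevalence.** A reader might put a 3-point band around 9.1 % to give a range for the yield. The 3 points are the precision sought from the planned survey. They are not the uncertainty of the earlier estimate, whose interval is not given.

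**Conclusion.** The point holds. The enlarged survey size contains no refusal allowance, whereas the figure it replaces does. If 1600 is the same kind of number as the 824, the plan's own prevalence and refusal rate give about 109–116 women, 55–58 per group, against the stated 146 and 73. If 1600 is completed interviews, the trial size is met but the number to approach is about 2,000–2,140 and is not stated.

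The first reading follows more naturally from the text, and the second remains open. The range within each reading comes only from the inflation convention. These counts use figures in the article and rest on taking the 9.1 % and 25 % at face value. The loss of power, from about 76–80 % to 63–67 % at 55 per group, is illustrative because it depends on a control-group rate that the article does not give.

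**What to change.** State in Sampling whether 1600 is women approached or completed interviews.

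- **If women approached:** restate the expected trial size as about 109–116 women (55–58 per group), according to the inflation convention used. Give the recalculated power together with the control-group rate on which it rests.
- **If completed interviews:** say so, and give the number of women to be approached, about 2,140 if dividing by 0.75 or about 2,005 if multiplying by 1.25.

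In both cases, name the convention used for the 25 % refusal.

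The cost is one recalculation and a few sentences. Restating the expected trial size needs no extra fieldwork. Keeping 73 per group when 1600 was meant as approaches would mean drawing roughly 400–540 more women (2,005 − 1600 = 405; 2,139 − 1600 = 539), which is best decided before streets and households are selected.

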### Inclusion criteria

Female residents in the two neighborhoods who are aged 18–60 years, literate, and without obvious cognitive impairments will comprise the target sample. Domestic violence behaviors will be investigated among women who have children of aged up to 18, husbands or partners, or both residing in the same household.

### Measurements

#### Participant sociodemographic characteristics

Information concerning ethnicity, age, education level, religion, occupation, marital status, and number of children will be obtained. Among women who are married or cohabitating, information regarding the duration of their relationship will be obtained along with the sociodemographic characteristics of their partners (e.g., age, education level, and occupation).

#### Alcohol consumption

Alcohol consumption will be assessed using the Alcohol Use Disorders Identification Test (AUDIT), a screening tool developed by the WHO [49] that consists of 10 questions: 3 concerning consumption amount and frequency, 3 regarding dependence symptoms, and 4 concerning personal and social problems related to alcohol abuse. The final score reflects the following alcohol consumption levels or patterns: abstainers/low risk (0–7 points), hazardous use (8–15 points), harmful use (16–19 points), and probable dependence (20–40 points). The AUDIT has been previously validated in several countries, including Brazil, and shows good sensitivity (mean = 0.90) and specificity (mean = 0.80) regarding the detection of harmful alcohol consumption [49, 50].

Information concerning the respondents’ use of any healthcare service over the previous 3 months, the approach of health professionals regarding respondents’ alcohol consumption, respondent participation in any treatment for alcohol consumption, and the respondents’ perceptions of their partners’ alcohol consumption will also be obtained.

#### Consumption of other substances

Information regarding the consumption of tobacco, marijuana, amphetamines, benzodiazepines, antidepressants, and cocaine over the three months preceding the interview will be obtained.

#### Health

A structured 15-question instrument concerning the respondents’ general health and the presence of specific diseases such as hypertension, diabetes, and heart problems will be administered.

#### Depression

The population-based screening scale for depression from the Center for Epidemiologic Studies (i.e., the CES-D) will be used. This screening instrument seeks to identify depressive symptoms within adult population-based studies [51]. Consisting of 20 items, its total score ranges from 0 to 60 points, with the higher scores indicating a greater amount of depressive symptoms. The cutoff of 16 points is often used to classify individuals as having possible depression. The CES-D has been previously validated for use in Brazil and shows satisfactory levels of reliability [52, 53].

#### Domestic violence

The Revised Conflict Tactics Scales (CTS2) will be employed to collect information on violence between intimate partners, whereas the Parent–child Conflict Tactics Scales (CTSPC) will be used to assess domestic violence by women against their children.

The CTS2 was designed to assess violence within couples, and it provides data on the respondent and her partner. This survey consists of 78 items, and each item is displayed in a set of two questions. The first question of each set refers to a possible behavior of the respondent, whereas the second refers to the same action but experienced by the partner. This instrument consists of 5 subscales that address the occurrence of negotiation, psychological aggression, physical violence, consequences of violence affecting the health of the respondent and her partner (i.e., injuries), and sexual coercion within the relationship. The CTS2 shows an internal consistency between 0.65–0.86 and an intra-observer reliability (kappa) above 0.75 when evaluated in Brazilian samples to assess its conceptual equivalence, semantic equivalence, and psychometric properties [54–56].

The CTSPC was designed based on the refinement of the previous instrument, and it addresses the parent–child relationship. This instrument is composed of questions regarding the occurrence of certain behaviors directed at children. Its 22 items are divided into three levels: nonviolent discipline (e.g., explaining errors and applying punishment), psychological aggression (e.g., swearing, screaming, threatening to kick the child out, or hitting), and physical assault (e.g., face slapping, throwing the child on the floor, or threatening with a knife); the latter was subdivided into corporal punishment, physical abuse, and severe physical abuse. The CTSPC had previously been cross-culturally adapted for use in Brazil; furthermore, prior work found that its internal consistency ranged from 0.49–0.68, and estimates of its intra-observer reliability (kappa) were above 0.75 [57, 58].

According to Straus [59] (the author of the CTS2 and CTSPC), these instruments investigate the occurrence of behaviors that, unlike emotions, attitudes, and beliefs, are less susceptible to distortions with regard to the interpretation of facts. Importantly, the methodological choice for these assessments reflects an understanding of domestic violence as a complex phenomenon that tends not to remain restricted to only one member of the family [58]. Furthermore, research indicates that violent acts are typically reciprocal, i.e., the respondent might be both the aggressor and the victim [60].

The information regarding alcohol consumption provided by the respondent and her partner during episodes of violence will also be incorporated by adapting the violence scales. After each CTS2 and CTSPC item, the interviewer will ask whether one of the involved individuals was under the influence of alcohol when the event occurred.

The CTS2 and CTSPC will be self-applied, whereas all of the other instruments will be administered to participants during interviews. Except for the CES-D, which refers to the events of the previous week, all of the instruments will be adapted to consider a time period of three months.

### Procedure

#### Study 1: Household survey

A researcher will approach the participants at their homes; all of the instruments will be administered there. The interviews will take approximately 30 min to complete and will be held in a place as private as possible to allow the interviewees to freely answer questions and increase the credibility of their answers.

The researchers will be properly trained women who will initially approach the participants to invite them to volunteer for the survey, delivering a document that describes the study and its objectives. The training of the team will consist of attending lectures on domestic violence, alcohol consumption, BIs, the project details, a clarification of the study’s procedures, and an explanation of the questionnaires. Furthermore, the importance of research ethics will be emphasized. The researchers will gain familiarity with the instruments by administering them to a colleague. Training will be provided on the application of a BI via videos and role-playing techniques.

To locate the women living in the randomly selected households, at least three visits will be made to each household. When a resident is not found at her supposed address, the researchers will seek information from the neighbors to identify the existence of any women who meet the eligibility criteria for the study and the best days and times to approach them.

#### Study 2: Random clinical trial

The data collection for Study 2 will be conducted concomitantly using the women detected in Study 1. Women with AUDIT scores equal to or above 8 will be considered as hazardous alcohol users and randomly allocated into one of two groups: the TG or the CG. The TG will receive a single BI after the instrument is administered, whereas the CG will not receive BI until after the end of the study.

The participants will be allocated using a list of random numbers. Three months after the BI, all instruments except for the sociodemographic questionnaire will be re-administered to both groups. Because of ethical reasons, a BI session will also be offered to the CG after the second evaluation, at the end of the study. Independent interviewers will perform the baseline and the follow-up interview.

#### The intervention

The BI will be performed at the participants’ households in accordance with the model proposed by Miller and Sanchez [61], the principles of which are summarized by the acronym “FRAMES”. This acronym stands for “Feedback” (provide information regarding the score obtained on the screening instrument), “Responsibility” (the patient must take responsibility for changing their behavior), “Advice” (guidance on issues related to the use of substances and coping strategies), “Menu of options” (a list of options or alternative behaviors to substance use), “Empathy” (putting one’s self in another’s shoes based on one’s own assumptions to try to understand their behavior), and “Self-efficacy” (patients’ belief in their ability to change).

The timing of the BI will be controlled, ranging from 15 to 40 min. After administering the procedure, the researcher will record the approach used and the participant’s behavior during the intervention.

### Ethics

This study has been approved by Ethics Committee of the Federal University of São Paulo (Universidade Federal de São Paulo; UNIFESP- registration number 0699/10). The study has also been registered in the Brazilian Clinical Trials Registry (ReBEC; registration number: RBR-7rjt4t).

All participants will receive information about the study, and their participation will be voluntary. Each participant will be required to sign an informed consent document. At the end of the interviews, all participants will receive an informational leaflet regarding the use of alcoholic beverages, as well as a guide concerning health services and psychosocial assistance in cases of violence and alcohol dependence. After the follow-up assessment is performed three months after the screening, the BI will be applied to participants in the CG. Women who score in the range of “probable alcohol dependence” (i.e., 20 points or more on the AUDIT) will be instructed to seek specialized treatment, regardless of the group to which they are allocated.

### Statistical analyses

Given the characteristics of the adopted sampling design, the data will be processed and analyzed using the statistical software STATA version 11.

Initially, exploratory bivariate analyses will be conducted to assess the associations between the variables of interest and the possible risk factors. Chi-square tests will be used to test the association between categorical variables, whereas Student’s *t*-test will be used to compare the means of continuous variables.

A logistic regression model will be used to examine the patterns of alcohol consumption with the response variable and the sociodemographic and health characteristics as explanatory variables. A separate logistic regression model will be used with the type of violence as dependent variable and the sociodemographic and health characteristics, and alcohol consumption patterns as explanatory variables.

The TG and CG will be compared using t-tests and generalized linear models with repeated-measures.

## Discussion

Both alcohol consumption among women and violence within the family are relevant public health problems which are mediated by cultural and contextual factors [20]. Despite the purported associations between these phenomena, studies providing information on their characteristics among women using community samples are scarce in Brazil [19, 21, 62].

This study includes a household survey with representative samples of two neighborhoods with different socioeconomic profiles in Brazil, a developing country where well-conducted household surveys remain rare. Although the cross-sectional design does not allow for the inference of causality, this approach will broaden the discussion on the relationship between alcohol consumption and violence, considering the individual and environmental aspects involved in these phenomena.

This study not only proposes to present a better understanding of violence in the lives of women (regardless of its association with alcohol consumption) but also expand the discussion regarding the possible public healthcare strategies and actions needed to prevent domestic violence and harmful alcohol consumption [1]. With regard to alcohol, the use of a BI in a community household setting represents a new method of prevention that could have indirect effects on domestic-violence-related problems.

We believe that this protocol has the potential to support supplementary studies aiming to promote knowledge regarding two of the most important public health problems from different perspectives: harmful alcohol consumption and domestic violence. Furthermore, we believe that the results of this study might influence both clinical practice and prevention efforts in the context of public health.

## Abbreviations

AUDIT: Alcohol use disorders identification test
BI: Brief intervention
CES-D: Center for epidemiologic studies depression scale
CTS2: Revised conflict tactics scales
CTSPC: Parent–child conflict tactics scales
DALYs: Disability-adjusted life years
IBGE: Brazilian institute of geography and statistics
WHO: World health organization
